## Objectives {7}

This trial evaluates the impact of an incremental P-WB curriculum delivered in French preschools, (1) after 24 weeks of program exposure in children 4 to 5 years old (during *moyenne section* in France: US Pre-K equivalent) and (2) 1 year later (end of *grande section:* US kindergarten equivalent; follow-up analysis).

Our primary objective is to assess the effects of the curriculum on P-WB-related measures of *Connection, Insight*, *Engagement*, *Positive Relationships*, and *Self-management*. Our secondary objective is to document the effects of the curriculum on measures of mental health, executive functioning, and school performance [51]. We hypothesize that the intervention will lead to more favorable outcomes on P-WB, mental health, and executive functioning measures after 24 weeks of program exposure, that these effects will be maintained 1 year later, and that school performance at the national evaluation 2 years later will be superior in children who received the intervention compared to the control group.

We also investigate heterogeneous effects according to teacher-level and children-level characteristics. In terms of teacher-level characteristics, we first investigate heterogeneity according to teacher P-WB since higher levels of P-WB are associated with higher impacts in various interventional settings [25, 47, 52, 75]. Second, we will use a machine-learning model to assess potential heterogeneous effects of the curriculum according to the teachers’ level of commitment in implementing the intervention (see the “Methods for additional analyses (e.g., subgroup analyses) {20b}” section for additional details). Higher levels of fidelity of implementation are associated with higher gains in children’s P-WB, mental health, and executive functioning [40, 56]. In terms of children-level characteristics, we investigate heterogeneity according to the initial levels of EF, *connection*, and problem behaviors. Lower pre-intervention levels of EF and *connection* are associated with higher gains in EF [38, 73] and *connection* [73] respectively. Similarly, higher pre-intervention levels of problem behaviors are associated with higher reductions in post-intervention problem behaviors [38].

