## Trial design {8}

The trial described in this protocol is a superiority two-armed cluster randomized controlled trial designed to evaluate the value-added of a P-WB promotion curriculum for pre-K children delivered by teachers, compared to teaching as-usual. Sixty-four pre-K classrooms from 50 different schools are randomly allocated to the intervention group or to the control group. In France, preschool classes can either include only students from one school year (here, Pre-K students only, “*moyenne section*” corresponding to 4-year-old children on average) or a mixture of children from Pre-K and kindergarten levels (kindergarten, hereafter K, students, or “*grande section*”, correspond to 5-year-old children on average). In the present sample, 36 classes included only Pre-K students, and 28 classes included a mixture of Pre-K and K levels students. In this context, as we expected potential differential effects according to the type of classroom, we stratified the sample by classroom type in order to compare treatment and control groups within the same type of classrooms. In practice, in the 36 classrooms with only Pre-K students, we randomly assigned 18 classrooms to the treatment group and 18 classrooms to the control group. In the 28 classrooms with a mix of Pre-K and K students, we assigned 14 classrooms to the treatment group and 14 classrooms to the control group. Overall, the treatment group and the control group are both composed of 32 classrooms.

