Description of the tools used and variables retained:School performanceIndicators of school performance are obtained 2 years after the beginning of the intervention, based on national evaluations taking place in the first and second years of primary school in France (*EVALAIDE* in Grade 1 and Grade 2). These evaluations target various literacy and math skills: reading out loud words, reading out loud text, understanding phrases while reading them, writing syllables, writing words, operating phonemes, recognizing letters, comparing letters, knowing letters’ names and sounds, understanding words, understanding phrases, understanding texts, reading numbers, writing numbers, visualizing numbers, comparing numbers, ordering numbers in sequence, resolving math problems, calculating mentally, adding numbers, subtracting numbers, and reproducing geometrical forms. *Mathematic skills, Reading skills*: based on these tests, we will create two outcomes corresponding to mathematics and reading skills.Standardized observations*Individualized Classroom Assessment Scoring System (InCLASS):* The InCLASS is a standardized naturalistic observation tool analyzing 3 to 5 years old children’s interactions in a classroom context [34]. It comprises 10 dimensions: (1) positive engagement with the teacher (which comprises the following indicators: attunement to the teacher, proximity seeking, and shared positive affect with teacher), (2) communication with the teacher (conversation initiated and maintained with the teacher, and variety of speech with the teacher), (3) teacher conflict (aggression, negative affect, attention-seeking behaviors, and non-compliance toward the teacher), (4) peer sociability (proximity seeking, shared positive affect, cooperation toward peers, and popularity), (5) peer communication (conversation initiated and maintained with peers, and variety of speech with peers), (6) peer assertiveness (positive initiation of interactions with peers and leadership toward peers), (7) peer conflict (aggression, negative affect, attention-seeking and confrontation toward peers), (8) engagement with tasks (sustained attention and active engagement in classroom activities), (9) self-reliance (personal initiative and independence in classroom activities), and (10) behavior control (patience, activity level matching expectations, and physical awareness) [13]. These dimensions have been grouped into four domains in a previous study using confirmatory factor analyses [13]: positive engagement with teachers (grouping positive engagement and communication with teacher), positive engagement with peers (peer sociability, peer communication, and peer assertiveness), positive engagement with tasks (engagement with tasks and self-reliance), and negative classroom engagement (teacher conflict, peer conflict, and the reversed score of behavior control). This tool has demonstrated solid inter-rater reliability, construct validity, and criterion validity [34]. *Positive engagement with teachers score, Positive engagement with peers score, Positive engagement with tasks score, Negative classroom engagement score:* Each dimension is rated on a 7-point scale, with higher score indicating higher frequency and/or quality of behavior within a dimension. Data from each of the observation cycles—collected by each data collector—are averaged to obtain final dimension scores. Mean score for the four domains are then calculated by averaging final dimensions scores within each of the four domains. Inter-rater agreement is calculated based on 12.5% of all observations, where the two data collectors independently observe the same child.Tasks*Challenging Situations task (CST):* An app-version of the full CST task is used to assess children’s emotional response in challenging interpersonal problems and ability to solve interpersonal problems [28]). Situation, emotion vignettes, and behavioral response vignettes are displayed on a tablet and responses are automatically registered. Emotional responses are composed of four different choices: happy, indifferent (“just ok”), sad, and angry. Behavioral responses are composed of four types of choices: a prosocial choice, an aggressive choice, an avoidant choice, and a dysregulated (“crying”) choice [27]. Examiners describe each situation picture and ask what the child would do in such a situation, by presenting response picture choices and asking the child to point at the picture corresponding to their emotion/behavior when/if the situation happens. Previous studies suggested that choosing sad emotion and prosocial behaviors on the CST constitutes adaptive behaviors that are linked with emotion knowledge and peer acceptance [28], and predicts classroom adjustment, pre-academic literacy skills, kindergarten readiness and academic achievement [26, 27, 81]. On the opposite, choosing aggressive response is associated with poor peer acceptance [28], poor classroom adjustment, and poor academic readiness [27]. *Adaptive responses score, Aggressive behavior score:* Along with previous studies [26, 81], the proportion of adaptive responses (Sad emotion + Prosocial behavior” responses) and aggressive behavior responses across the six vignettes (ranging from 0 to 6) are calculated.*Emotion matching task-expressive knowledge:* The expressive knowledge sub-task of the Emotional Matching Task (EMT) measures 3 to 6- years-old children expressive emotion knowledge – i.e., the ability to recognize and label expressions of others’ emotions (based on Izard test [46, 55];). A sample of 12 colored photographs representing ethnically-diverse children with emotional facial expression are presented on a tablet screen: happiness, sadness, fear/surprise, anger, and mixed (anger/sadness). Children are asked each time what the child on the picture is feeling [55]. The EMT has demonstrated good criterion validity, strong reliability and construct validity [55], and preliminary evidence for cross-cultural validity has been found [3]. *Expressive emotional knowledge score:* Each child verbal responses are assigned to a score of 0 (= incorrect response), 1 (=accepted response), or 2 (=correct response). Accepted verbal responses are pre-determined and listed in a table before test sessions using the instruction manual. All items are summed to obtain the total score, with higher score indicating better expressive emotion knowledge.*Executive functioning battery:* We use an app-version of the EF battery (“*EF Touch*”), a battery of six EF tasks designed for preschool children from 3 to 5 years, which was found to show good criterion validity [83]. Each response is automatically registered on a computer communicating with the tablet. Analyses of dimensionality show that performance on EF tasks is best characterized by a single EF factor [83]. The Houses, Pick the Picture and Something the Same tasks, when combined, best approximate an EF latent variable underlying performance on all the six tasks [84]. We therefore selected these three tasks to assess children’s EF within a single EF latent factor model. Finally, following the suggestion of Willoughby et al. [84], only two randomly selected tasks out of three are administered to each child using a planned missing design, in order not to overload attention capacities of children and to reduce global test burden. Score for the missing parameter is estimated through an imputation procedure.*Houses game (also named Working Memory Span game):* This task assesses working memory span. Children are presented with houses in which are located a line-drawing animal and a color dot. They are asked to name both the animals and the colors in each of the houses. Then, animals and color dots disappear from houses. Children have to recall either which animal *or* which color was in the target house, thus holding in mind two pieces of information and activating one of them (i.e., animal name) while overcoming interferences from the other (i.e., color name) [84]. Task becomes increasingly difficult as the number of houses on the screen increases (from one to three houses).*Pick the Picture (PTP) game:* This is a self-ordered pointing task assessing working memory. In this task, children are asked to touch once each picture appearing on the screen, so that all of the pictures “get a turn” [84]. Between each touch, location of pictures is changed in a randomized order. Difficulty of the task increases as the number of pictures increases (from two to six pictures).*Something’s the Same (STS) game:* This task evaluates cognitive flexibility. For each item, children are asked to shift their attention from one dimension of similarity to another dimension of similarity [84]. Initially, they are presented with two pictures that share one dimension of similarity (e.g., color, shape, size, etc.). Then, a third picture is presented, and children have to tell how this new picture is similar to one of the original pictures. This last picture always shares a different dimension of similarity with one of the original pictures. In the second part of the game, all pictures are presented at once and children have to identify two different dimensions of similarity.*Working memory span score 1 (Houses), Working memory span score 2 (Pick the picture), Cognitive Flexibility Score*: for each EF battery game, each response is coded into a dichotomous variable (0 = incorrect response, 1 = correct response). The total score is a proportion ranging from 0 to 1, with 0 indicating no items correct and 1 indicating all items are correct.*Peer acceptance task:* The peer acceptance task measures how a particular child is accepted and liked by his peers in his/her class. It is a peer rating measure inspired by Asher et al. (1979) sociometric procedure [14]. Children are presented with photos of their classmates. After identifying classmates on these photos, they are asked to sort each photo of classmates into three envelopes: happy smiley for “I really like to play with this child”; neutral smiley for “I kind of like to play with this child”; unhappy smiley for “I don’t like to play with this child”. Answers are coded 3, 2, and 1 respectively. This procedure shows adequate reliability and validity [14]. *Peer acceptance score*: After testing each child, we assess how many times a child photo is put in each envelope: a mean score is calculated by summing up the score on each trial and dividing by the number of children in the classroom minus one. The final score indicates how much a child is accepted by his peers, with higher scores indicating higher levels of acceptance.*Sharing task:* This task evaluates child sharing. The sharing task used in this study is a sub-section of the task designed by Flook et al. [38], divided into two trials. For each trial, children are presented with 10 stickers. They are told that they can keep as many stickers as they want for themselves and share as many as they want with another child. They then separate stickers between two different envelopes (identified with the photo of the assessed child and the photo of the other child). In the first trial, the other child is the one identified by the assessed child as his/her most-liked classmate, and in the second trial, the other child is the one identified as the least-liked classmate. Sharing ability has been shown to differ between groups that received an SEL intervention compared to control group [38]. *Sharing proneness score*: 20 minus the total number of stickers (ranging from 0 to 20) put in the “me” envelope across the two trials is calculated. Higher scores indicate higher levels of sharing tendencies.Teacher-rated questionnaires*Commitment to implement:* Teachers in the intervention group are asked about their commitment to implement the program using a single item: “I feel motivated to use the program/strategies in my classroom”. Previous study indicates that this item is a valid indicator of teacher commitment to implement various evidence-based programs, regarding construct validity and convergent validity with other measures of commitment and with commitment predictors [22]. Teachers in the intervention group are also asked whether they liked the training, whether they found it useful, whether they found the content of the program useful, whether they liked the content of the program, and whether their students liked the content of the program. These items are rated on a 5-point Likert scale (from 1= “strongly disagree” to 5 = “strongly agree”). *Commitment score*: We will construct a standardized commitment score based on these previous items. Higher score indicates higher commitment to implement. As the psychometric properties of this score have not been validated, we will check the internal validity of the constructed score using Cronbach’s Alpha.*Preschool and kindergarten behavior scale (PKBS)- Social skills:* The PKBS social skills [54] is a teacher-rated scale assessing preschool and kindergarten children’s social skills. The French version of the scale is divided into 5 subscales [20]: The first subscale, “social interaction’ consists of 10 items that reflect behaviors and attitudes necessary to develop and maintain good relationships and friendship with others (such as defend others’ rights, helping others), “participates in classroom or family discussions,” “shows affection for other children,” or “tries to understand another child’s behavior.” The second subscale consists of six items and reflects components of “agreeableness with peers,” such as “plays with several different children,” “makes friend easily,” or “smiles and laughs with other children.” The third subscale, “compliance,” relates to respect for adult authority and social norms, such as “follows instructions from adults,” “follows rules,” or “uses free time in an acceptable way.” The fourth subscale, “cooperation with peers,” describes behaviors such as “shares toys and other belongings” or “gives in or compromises with peers when appropriate.” Finally, the fifth factor, labeled “autonomy,” is composed of items such as “works or plays independently,” “adapts well to different environments,” or “attempts new tasks before asking for help.” *Total PKBS Social Skills Score, PKBS Social interaction score, PKBS Agreeableness with peers score, PKBS Compliance score, PKBS Cooperation with peers scores, PKBS Autonomy score; PKBS functional level categorical score*: The 34 items are rated on a 4-point Likert scale ranging from 0 (= Never) to 3 (= Often). Total raw scores and raw scores for each subscale are calculated by adding scores of each item, with higher scores indicating better social skills. For 5–6-year-old children, total raw scores are divided into 4 functional level categories based on child age: “high functioning” (scores 95 to 102), “average” (scores 76 to 94), “moderate deficit” (scores 59 to 75), and “significant deficit” (scores 0 to 58) to compute a functional level categorical variable.*Strengths and difficulties questionnaire (SDQ)-extended teacher version*: The SDQ-extended teacher version is a scale used to measure children’s externalized symptoms, internalized symptoms, and pro-social behaviors [42]. It is divided into five factors of five items each: emotional symptoms, conduct problems, hyperactivity-inattention, peer problems, and prosocial behavior. At the end of the questionnaire, 4 items explore impacts of difficulties (overall distress, social impairment, learning impairment, and burden for teacher and classroom) [41]. The SDQ displays satisfactory reliability and validity [42] and although its factor structure in French language remains uncertain [15, 16], the SDQ French version shows satisfactory reliability and content validity for the total difficulties score [16]. *SDQ total difficulties score, SDQ impact score*: The 25 items are statements rated on a 3-point Likert scale indicating to what extent each statement applies to a target child, with 0 = Not true, 1 = Somewhat true, 2 = Certainly true. All factors except Prosocial behavior are summed in a Total difficulties score. Items relative to impact of difficulties are coded from 0 to 2, with 0 corresponding to no impact or little impact, 1 corresponding to “Somewhat impactful”, and 2 to “Very impactful”. An impact total score ranging from 0 to 8 is then generated by summing these items. Higher scores indicate higher levels of difficulties and higher level of impact.*Student-teacher relationship scale-short form (STRS):* The STRS-short form is a teacher-rated scale exploring teachers’ perspective on their relationship with a designed child in their classroom [60]. The scale comprises two distinct factors, one measuring the degree to which teacher-child relationship is characterized by warmth, positive emotions and open communication (closeness), and the other measuring the degree to which the relationship is characterized by negative emotions and interactions (conflict). This scale possesses excellent psychometric properties across multiple samples [60]. The validation of the French version is ongoing [21]. *STRS Closeness score, STRS Conflict score:* The 15 items (8 items assessing Closeness, 7 items assessing Conflict) are scored using a 5-point Likert scale ranging from 1 (= Definitely does not apply) to 5 (= definitely applies). Total scores are then calculated for each factor.Teacher personal well-being P-WB:*Comprehensive inventory of mindfulness experience (CHIME):* The Comprehensive Inventory of Mindfulness Experience (CHIME) is a self-report multidimensional scale measuring “dispositional” (or “trait”) mindfulness in adults with or without knowledge or previous contact with mindfulness [9, 53]. It captures the following eight dimensions of “trait” mindfulness: awareness of internal experience, awareness of external experience, acting aware, self-acceptance and non-judgment, non-reactivity, openness and non-avoidance, ability to relativize, and insight. The CHIME exhibited good reliability and satisfactory construct validity [9]. The validated French version of the scale used in this study showed highly satisfactory psychometric properties as well [71]. *CHIME Total score:* The 37 items are rated on a 6-point Likert scale (from 1 = “fully applies” to 6 “does not apply at all”). Total score is calculated by inverting each item score and adding all inverted score. Higher scores indicate higher proneness to experience mindfulness in everyday life.*Warwick-Edinburgh mental well-being scale (WEMWBS):* The Warwick-Edinburgh mental well-being scale (WEMWBS) is self-report single-factor measure composed of positively worded items related to positive mental health and well-being [74]. It covers a wide-range of concepts associated with positive mental health, including hedonic and eudemonic well-being, satisfying personal relationship, and positive functioning. The original version displayed good content validity and reliability [74], and the French version used in this study showed good internal consistency, stability and construct validity [77]. *WEMWBS Total score*: The 14 items are rated on a 5-point Likert scale (from 1= “never” to 5 = “always”), with high score indicating higher mental well-being.*Satisfaction with professional life scale (Echelle de Satisfaction de Vie Professionnelle; ESVP):* The ESVP scale is a unidimensional French short self-report measure of general professional life satisfaction derived from the Satisfaction with Life scale from Diener et al. (1985) [29, 39]. It displays adequate level of internal consistency and temporal stability, and good construct validity [39]. *ESVP total score*: The 5 items are rated on a 7-point Likert scale (from 1= “strongly disagree” to 7 = “strongly agree”), with higher scores indicating higher professional life satisfaction.

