### Methods for additional analyses (e.g., subgroup analyses) {20b}

We will estimate the effects of the intervention on the children’s and teachers’ outcomes listed in the “Outcomes {12}” section based on the following characteristics:Girls (for the children)Level of experience of the teachers (according to the median)Age of the teachers (according to the median)Initial levels of EF, connection, and problem behaviors of the childrenMulti-level classesTeachers predicted to have a high degree of commitment with the intervention by a machine learning model

According to the data collection plan detailed in this paper, we will ask questions about treatment-group teachers’ commitment with the intervention (see Plans for assessment and collection of outcomes {18a} section) and will average teachers’ answers into a standardized score of their commitment with the intervention. Then, we will run a Lasso regression [7] of that score on all the socio-demographic variables and the outcomes listed in the “Outcomes {12}” section measured at baseline, on the square of those variables, and on the products of all the pairs of variables. We will then use the Lasso regression to predict the commitment score of every teacher included in the experiment, hence including teachers in the control group. Finally, teachers predicted to have a high degree of commitment with the intervention will be those with a predicted score above the median. To compute predicted commitment with the intervention for treatment group teachers, we will use a leave-one-out method, as suggested by Abadie et al. [1]. It may however be the case that we are not able to predict the teachers’ commitment score very well, in which case, undertaking that third subgroup analysis would not be informative. If the Lasso regression does not select any variable, or if the R2 of the OLS regression of the commitment score on all the variables selected by the Lasso regression is below 0.1, we will not conduct that subgroup analysis.

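### In the predicted-commitment subgroup, the R2 branch of the stop rule gives no protection against noise; separately, teacher P-WB is missing from the moderator list

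*Protocol article*

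**What the plan says.** The section on additional analyses {20b} builds a commitment score for intervention teachers and fits a "Lasso regression [7] of that score on all the socio-demographic variables and the outcomes listed in the" Outcomes {12} section, measured at baseline, and also "on the square of those variables, and on the products of all the pairs of variables". The fitted model predicts commitment for all teachers in both arms, and teachers above the median prediction form the high-commitment subgroup. Predictions for intervention teachers are made by leave-one-out.

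The section accepts that commitment may be hard to predict and that the subgroup would then tell the reader little. Its safeguard has two branches. The subgroup is dropped if the Lasso selects no variable, or if "the R2 of the OLS regression of the commitment score on all the variables selected by the Lasso regression is below 0.1". Leave-one-out is specified for the predictions only, not for this R2.

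The score exists in one arm only: "Teachers in the intervention group are asked about their commitment to implement the program using a single item" (section {18a}). On arm size, Trial design {8} says: "Overall, the treatment group and the control group are both composed of 32 classrooms".

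On moderators, Objectives {7} says of teacher-level characteristics that "we first investigate heterogeneity according to teacher P-WB since higher levels of P-WB are associated with higher impacts". The list in {20b} has child sex, teacher experience, teacher age, children's initial EF, connection and problem behaviors, multi-level classes, and predicted commitment. Teacher P-WB is not on it.

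**The concern.** An R2 computed on the data that chose the predictors measures how hard the search was as well as how well commitment is predicted. With several hundred candidates and about 32 teachers, chance alone supplies variables that fit well. A cut-off of 0.1 on that quantity looks like a test of predictive value but is met almost automatically.

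If so, the plan has one working safeguard where it appears to have two. When the remaining one fails, teachers are split at the median of a score unrelated to commitment, and the two halves are reported as likely high and low commitment. This is the situation that {20b} says it wants to avoid.

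The omission of teacher P-WB is a separate matter: the teacher moderator named first in the objectives has no entry in the section that lists the moderators.

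**Working it through.** **Inputs**
- Training sample: "we randomly assigned 18 classrooms to the treatment group and 18 classrooms to the control group" among Pre-K-only classes and "we assigned 14 classrooms to the treatment group and 14 classrooms to the control group" among mixed classes (Trial design {8}). So 18 + 14 = 32, which reproduces the stated arm size. This assumes one teacher per class, all responding.
- Base predictors: the outcome tables under Outcomes {12} give 15 primary variables (4 connection, 2 insight, 2 engagement, 3 positive relationships, 4 self-management) and 5 secondary ones (2 SDQ, 3 EF). School performance has no baseline value. That makes 20, each taken as one value per teacher. The number of socio-demographic variables is not given; 0 to 10 is assumed.
- Threshold: 0.1, given without a derivation, so there is no figure to reproduce.

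**Number of candidate terms**

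With m base variables there are m + m + m(m-1)/2 terms:
- m = 20: 20 + 20 + 190 = 230
- m = 25: 25 + 25 + 300 = 350
- m = 30: 30 + 30 + 435 = 495

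So 230 is the floor, before any missing-value indicators.

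**Exact benchmark for the threshold**

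For one noise predictor fixed in advance, R2 = 0.1 at n = 32 corresponds to F = 0.1 / (0.9/30) = 3.33 on 1 and 30 degrees of freedom. P(R2 ≥ 0.1) is then 7.8%. For the best of k independent noise predictors, P(R2 < 0.1) = (1 - 0.078)^k:
- k = 230: about 8e-9
- k = 350: about 5e-13

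Squares and products are not independent of their parents, so this is a guide only. The simulation below uses the actual structure.

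**Simulation of the written rule under pure noise**

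Settings: n = 32; m = 20, 25 or 30 with all squares and products; predictor correlation 0 or 0.3; a normal score or a six-item Likert mean; 1,000 to 2,000 runs per setting. The article does not state the penalty, so three were tried.

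| Penalty | Stopped by no selection | Stopped by R2 < 0.1 once something is selected | Noise subgroup goes ahead |
|---|---|---|---|
| 10-fold CV minimum | 50-53% | 0 of about 3,900 | 47-50% |
| CV one-standard-error | 91-92% | 0 of about 670 | 8-9% |
| Plug-in | 99.9-100% | almost never reached | 0-0.1% |

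Under the two cross-validated penalties, when something was selected, the median number of variables was 3 to 6, the median in-sample R2 was 0.62 to 0.76, and the lowest R2 was about 0.17.

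**Simulation of the leave-one-out version**

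Leave-one-out R2 = 1 - Σ(y_i - ŷ_(-i))² / Σ(y_i - ȳ_(-i))², where ŷ_(-i) and ȳ_(-i) are computed without teacher i and the Lasso is reselected and retuned each time. With m = 25, 350 terms, correlation 0.3, the CV-minimum penalty and 200 noise runs:
- written rule goes ahead: 51.5%
- leave-one-out R2 ≥ 0.1: 4.5%
- among runs that the written rule passes: median in-sample R2 0.57, median leave-one-out R2 -0.06

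**Moderators**

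Objectives {7} puts teacher P-WB first among the teacher-level moderators and predicted commitment second. {20b} carries the second and not the first, although section {18a} collects CHIME, WEMWBS and ESVP from teachers.

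**The case against.** The strongest reply is that the rule has two branches and the other one works. A reader might infer from the inert threshold that the rule as a whole cannot stop a subgroup built on noise. The document does not support that. The no-selection branch stops about half of noise datasets under a CV-minimum penalty and nearly all under a plug-in penalty. The penalty is a detail that an article may leave to the full plan or to the Lasso method it cites, so the overall failure rate cannot be fixed from this text. What stands against the plan is narrower: under none of the penalties tried did the R2 branch add anything.

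A second reply is that leave-one-out predictions already keep a teacher's own commitment score out of that teacher's classification. That is true and limits the harm to an uninformative, mislabelled split, but it does not make the stop rule detect poor prediction.

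A third reply is that the stricter rule also loses real signal. In a simulation with 23 base variables, 299 terms, correlation 0.3, 5-fold cross-validation and two true predictors explaining 30% of commitment, the written rule ran the subgroup in about 65% of 240 runs and the leave-one-out rule in about 15%. This cost is real. Many of the dropped models predicted poorly out of sample, so dropping them can be defended, but the authors should adopt the rule knowing it.

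On teacher P-WB, a reader might infer that the analysis has been abandoned. The article shows only that two of its sections disagree.

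**Conclusion.** The point holds in limited form. The R2 < 0.1 branch is inert: with at least 230 candidates and about 32 teachers, noise exceeds 0.1 essentially whenever anything is selected. Protection rests on the no-selection branch alone, so a noise-based subgroup goes ahead in anything from about 0% to about 50% of cases, depending on the unstated penalty. The inertness held across every candidate count, correlation and score type tried. The pass-through rates rest on those settings and on one responding teacher per class.

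The reach is small. This is one additional subgroup analysis. It would be wrong to infer that the ITT results are in doubt, because the stop rule plays no part in them.

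The missing teacher P-WB moderator is a plain inconsistency between {7} and {20b} and does not depend on the Lasso argument.

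**What to change.** In {20b}, keep the no-selection branch and replace the R2 branch. Run the subgroup only if the leave-one-out R2 of predicted versus observed commitment among intervention teachers is at least 0.1, with variable selection and penalty tuning repeated without the left-out teacher. It would help to name the penalty rule in the same sentence, since it governs how often the no-selection branch acts.

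In the same section, add baseline teacher P-WB (WEMWBS, CHIME, ESVP) to the moderators. The form, interaction or median split, can follow the other teacher moderators.

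No new data are needed, and leave-one-out predictions are already planned. The added work is redoing selection and tuning in each fold. The real cost is that the commitment subgroup will be dropped more often, including under a moderate true signal, and the text should say so.
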